**Figure 2 figure2:**
[figure not shown]
Depiction of the Holm perfusion zones [21]. Zone I is well recognized for being the most richly perfused as it contains the perforator vessels. The use of this zone during deep inferior epigastric perforator (DIEP) flap breast reconstruction surgery may provide optimal tissue flap perfusion.

Our secondary outcomes include (1) tissue oxygenation at baseline (preoperatively), intra-operatively and 1, 2, 4, 8 hours postoperatively, as well as the morning of postoperative days 1 and 2; (2) the amount of intravenous fluids (crystalloids, colloids, blood products) and vasopressors (eg, phenylephrine, ephedrine, norepinephrine, etc) administered intraoperatively and up to 4 hours postoperatively; (3) the need for intraoperative surgical vascular reintervention (ie, reanastomosis); (4) laboratory measures including perioperative pH, serum lactate, and hemoglobin measures; (5) incidence of postoperative nausea and vomiting; (6) hospital length of stay; (7) any postoperative complications including infection, hematoma, and those resulting from flap malperfusion (ie, partial/total flap loss and fat necrosis); (8) the need for postoperative intervention for flap-related issues; (9) overall patient satisfaction; and (10) days alive and out of hospital, all up until 30 days postoperatively.

## Methods

### Ethical Considerations

This study received institutional ethics board approval (ANAE-341-19) on May 16, 2019, and Health Canada approval (control no 228403) on July 8, 2019. Moreover, it was registered on Clinicaltrials.gov (NCT04020172) on July 12, 2019. This study is being completed in compliance with the current protocol and the Guidelines for Good Clinical Practices. All data collected will be retained for 15 years in a form identified only by study identification numbers linked to the patient’s identity through a master list kept separate from the data in a locked cabinet. Only study investigators and governing bodies for regulatory inspections/trial monitoring will have access to the confidential patient data. Should any significant protocol modifications be required that may impact participants’ provision of consent or safety, this will be immediately shared with the participants, the ethics board, and Health Canada as appropriate. Such changes will also be documented on the Clinicaltrials.gov registry.

### Participants and Recruitment

#### Overview

Patients scheduled for elective unilateral or bilateral delayed or immediate DIEP flap surgery at a medium-sized academic center will be recruited. Eligible patients will be approached at their preoperative surgical visit with the plastic surgeon ([name]). If patients are willing to participate, a research team member will obtain written informed consent after their assessment by the attending surgeon (Multimedia Appendix 1). In all cases, the anesthesiologist will be made aware of the patient’s potential study involvement should there be any medical reasons warranting study exclusion.

#### Sample Size

There are few similar studies in the literature on which to base a valid sample size calculation. However, 1 randomized controlled trial (RCT) [15] compared 3 arms, two of which are similar to what we propose to study in terms of pharmacological intervention (ie, dobutamine/dopexamine) versus none (standard of care). Eight hours postoperatively, they noted a 1.75 kPa increase in cutaneous tissue oxygen partial pressure (PtO_2_) in their stroke volume (SV) + dopexamine arm as compared to a 0.50 kPa increase in the SV-only arm. Using an SD of 1.0, α of 0.05, and a power of 80%, only 11 cases would be required per arm for these differences to attain statistical significance. However, this sample is rather small for valid statistical analyses [22], and because our groups are not identical to those available in the literature, we propose to increase the sample size to 20 per group. Notably, given that their SV group is tightly regulated (and therefore, likely superior) compared to our standard of care group, our sample size estimation is likely overly conservative.

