### Objectives and Outcome Measures

The main objective is to determine whether the use of minimally invasive CO monitoring to guide intravenous fluid administration, combined with low-dose dobutamine infusion (via a treatment algorithm), will increase overall tissue oxygenation in patients undergoing DIEP flap surgery. The primary outcome is tissue oxygenation, measured via near-infrared spectroscopy (NIRS), 45 minutes following vascular reanastomosis of the DIEP flap within the perfusion zone farthest from the perforator vessels. This zone is the most vulnerable surgical area to ischemia and therefore the most likely to reflect the potential benefits of the proposed intervention. In the case of bilateral DIEP flaps, this zone will be assessed in both the left and right breasts. The zonal blood supply for DIEP flaps is depicted by Holm (Figure 2) [21]. Zone 1 includes the perforator vessel and is thus the most reliably perfused portion of the flap, while any flow across the midline can be less reliable than ipsilateral flow depending on the location of the perforators in zone 1. As aforementioned, the primary outcome will be tissue oxygenation within the zones farthest from the perforator vessels.

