#### Approved Protocol

A tissue oximeter device (SnapshotNIR; Kent Imaging) will be used for all patients. This is a portable noninvasive monitor that measures tissue oxygen saturation using NIRS technology with the capability of saving images to allow for subsequent analyses. Measurements will be taken by holding the monitor at a standardized (30 cm) distance from the skin area where the oxygen levels are to be measured. Upon admission to the OR, preoperative baseline measurements (with patients breathing ambient air without supplemental oxygen) will be recorded over the abdominal flap tissue, followed by recordings immediately postinduction, 1-hour postinduction, when the abdominal flap is free (and still perfused by the chosen perforator arteries), before clamp removal postarterial reanastomosis, and 45 minutes following reanastomosis. All research personnel dedicated to this study will receive prestudy training on the perfusion zones and study outcomes to ensure that oxygenation measures are consistently taken from the same surgical region in relation to the perfusion zones (as described in Figure 2) throughout each case. In addition, the surgical team, led by authors [name], will assist with guiding the intraoperative oxygenation measurements with respect to flap location. However, the surgical team and attending anesthesiologist will be blinded to the Kent oxygenation measurements throughout the perioperative period, and surgery will be guided as per the standard of care. The ischemic period during which the flap is transferred (reflected by a fall in the oxygen saturation of the flap [23]) as well as the time of flap revascularization (characterized by increased oxygen saturation [23]) will be recorded. Upon completion of the surgical procedure, another NIRS-based monitor (Somanetics INVOS 5100C Cerebral/Somatic Oximeter; Medtronic) may be applied to the freshly reconstructed graft at the surgeon’s discretion. If deemed appropriate, a sticker will be applied over the flap for continuous graft oxygenation monitoring up to 48 hours postoperatively. However, if the surgeon requires the entirety of the graft to be exposed for visual monitoring (as per the standard care), a sticker/sensor will not be applied. Nevertheless, postoperative measures will be routinely recorded at 1, 2, 4, and 8 hours postoperatively, as well as on the morning of postoperative days 1 and 2 using the Kent device. All measures will be consistently taken at the same location [24]. Note that continuous intraoperative monitoring with the Somanetics INVOS Oximeter is not possible, as the sensors cannot be sterilized.

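### The sample size is derived from a different outcome, so the claim that it is probably conservative has no support for flap saturation; 20 per arm has 80% power only for about 0.91 SD

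*Protocol article*

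**What the plan says.** The Sample Size section of the protocol article opens by admitting that few comparable studies exist. It then takes two arms of one randomized trial. At eight hours after surgery, in the arm given stroke-volume guidance plus dopexamine, "they noted a 1.75 kPa increase in cutaneous tissue oxygen partial pressure", "as compared to a 0.50 kPa increase in the SV-only arm". The calculation reads: "Using an SD of 1.0, α of 0.05, and a power of 80%, only 11 cases would be required per arm". The number is then raised to 20 per group, because 11 is small and because the groups are not the same as those in the literature. The section closes with the view that "our sample size estimation is likely overly conservative". Its reason is that the cited comparator was tightly managed and so probably did better than this trial's standard-care arm will.

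The primary outcome is defined in Objectives and Outcome Measures as tissue oxygenation by near-infrared spectroscopy, "45 minutes following vascular reanastomosis of the DIEP flap within the perfusion zone farthest from the perforator vessels". The Approved Protocol section says that the device "measures tissue oxygen saturation using NIRS technology". The Statistical Analysis section compares tissue oxygenation by independent-samples t test, or by Mann-Whitney U if the data are not normal, at P<.05.

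**The concern.** The sizing inputs and the primary outcome are different quantities. One is a change in oxygen tension in skin, in kPa, at eight hours. The other is oxygen saturation in the most ischemia-prone part of a free flap, 45 minutes after reanastomosis. The article gives no expected difference and no SD for flap saturation, and no source for the SD of 1.0. The section's caveat covers the groups but not the outcome.

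This matters because the closing sentence tells the reader that the trial is more than large enough. The Discussion makes a multicenter trial depend on showing better oxygenation. If the result is not significant, the weight it can bear depends on which effects the trial could have detected. A reader who takes the sample size as conservative will credit a null result with more than 40 patients can support.

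**Working it through.** **Inputs.** All come from Sample Size unless noted: increases of 1.75 and 0.50 kPa; SD 1.0; α 0.05, sidedness not stated; power 80%; 20 per group. The test, a two-sample t test, comes from Statistical Analysis.

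**1. Reproduce the plan's figure.**

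- Standardized difference: d = (1.75 − 0.50)/1.0 = 1.25.
- Normal approximation, two-sided: n per arm = 2 × (1.960 + 0.842)² / 1.25² = 10.05, rounded up to 11.
- A one-sided calculation gives 8, so the plan is evidently two-sided.
- Exact noncentral-t power is 79.6% at 11 per arm and 83.3% at 12.

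The stated 11 is therefore reproduced.

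**2. Power at 20 per arm on the borrowed inputs.** With d = 1.25, power is 97.1%. It depends on the unsourced SD:

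| SD (kPa) | d = 1.25/SD | Power at 20 per arm |
|---|---|---|
| 1.0 | 1.25 | 97% |
| 1.2 | 1.04 | 89% |
| 1.5 | 0.83 | 73% |
| 2.0 | 0.625 | 49% |

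Power for 1.25 kPa stays at 80% or more only while the SD is at most 1.25/0.909 = about 1.37.

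**3. What 20 per arm can detect on any continuous outcome.** The noncentrality is d × √(20/2), with 38 degrees of freedom and two-sided 5%.

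- 80% power: d = 0.909 (normal approximation 2.802 × √(2/20) = 0.886).
- 90% power: d = 1.052.
- Mann-Whitney under normality, assuming an efficiency of 0.955: about 0.93 for 80% power.

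| True difference (SD) | Power at 20 per arm |
|---|---|
| 0.5 | 34% |
| 0.6 | 46% |
| 0.7 | 58% |
| 0.8 | 69% |
| 0.9 | 79% |
| 1.0 | 87% |

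Power crosses 50% near 2.024 × √(2/20) = 0.64 SD. The same product is the approximate half-width, in SD units, of the 95% confidence interval for the difference.

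**4. In saturation points.** The document gives no SD for saturation. Assuming 5, 10 or 15 points, 0.909 SD is 4.5, 9.1 or 13.6 points.

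**5. Does the conservatism argument reach the outcome?** A weaker control arm could widen the contrast, so the argument points the right way for the comparator. It does not bear on how a 1.25 kPa change in skin tension maps to flap saturation, on how variable saturation is in the farthest zone, on the earlier time point, or on dobutamine in place of dopexamine.

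**The case against.** The strongest reply is that the plan is open about its weak basis. It says that few studies exist, raises 11 to 20 (an increase of 9/11, or 82%), hedges with the word likely, and gives a reason that is right as far as the comparator goes. On its own inputs 20 per arm gives 97% power. Tissue oxygen tension is a related quantity and a reasonable proxy when nothing closer is available. All of this stands. None of it reaches the outcome, which is where the inference fails.

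Four stronger readings are tempting, and the document does not support them:

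- *The calculation is wrong.* It is not; 11 per arm follows from the inputs.
- *The plan claims 80% power at 20 per arm.* It does not. The text attaches it to the smaller number: "a power of 80%, only 11 cases would be required per arm for these differences to attain statistical significance". No power is stated for 20.
- *The trial would usually miss moderate effects.* This goes too far. Power is 58% at 0.7 SD and 69% at 0.8 SD, and nothing in the document shows which effect size is plausible.
- *The investigators will read a null result as no effect.* The Discussion commits only to what follows a positive result. The risk lies in how a reader would use the conservatism claim.

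Two further arguments are too weak to rely on. Bilateral flaps contain only zones 1 and 2, so the farthest zone is not the same in every patient, but most cases are expected to be unilateral and no variance figure is given. The cited figures are changes, whereas no change score is stated here; under randomization that affects the SD, not the expected difference between arms.

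**Conclusion.** The point holds as a problem of sample-size assumptions, not of arithmetic. The inputs do not transfer to the primary outcome, so the statement that the size is probably conservative is unsupported. What can be said is that 20 per arm has 80% power for about 0.91 SD, and that differences below about 0.64 SD would be missed more often than found. At 0.5 SD the miss rate is about two in three (1 − 0.338 = 0.66).

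These figures assume a two-sided 5% t test, one value per patient, roughly normal data with equal variances, and all 20 patients per arm analyzed. The figures in saturation points rest on assumed SDs. The document does not show whether the trial is too small or large enough, because it gives neither a plausible effect nor an SD for flap saturation.

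**What to change.** Keep 40 patients. In Sample Size:

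- Delete the conservatism sentence.
- Describe the kPa calculation as indirect support, and say that its outcome, unit, site and time differ from those of this trial.
- State that 20 per arm gives 80% power for a difference of 0.91 SD in flap saturation at 45 minutes (two-sided 5% t test).

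Before unblinding, compute the SD of the 45-minute reading over all completed patients without regard to group, on the same per-patient value that will be analyzed, and report 0.91 times that SD in saturation points. The article reports 34 patients completed and investigators still blinded, so this is feasible at that status. A group-blind SD slightly overstates the within-group SD if there is a true effect: with equal arms the factor is √(1 + d²/4), which at d = 0.91 is √1.207, or about 1.10.

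State in advance that a non-significant result will be interpreted by its 95% confidence interval against that detectable difference.

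The cost is a few lines of text and one blinded calculation. The stated figure becomes less favorable than the present wording suggests. No more patients are needed, and neither the design nor the primary test changes.

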### Study Design, Randomization, and Blinding

#### Overview

This is a prospective RCT. A total of 40 participants will be randomized to one of 2 groups (n=20 per group) using a computer-generated randomization prepared by the institutional biostatistician. Patient randomization will be concealed in envelopes and opened only by the research staff (not otherwise involved with data collection) and/or the attending anesthesiologist prior to anesthesia induction. Blinding will be maintained until study completion and verification that all outcome data have been successfully collected for all study participants.

#### Surgical Procedure

Patients will be marked in the preoperative holding area for an abdominal-based free-flap breast reconstruction. All procedures are planned as a DIEP reconstruction. For most flaps, the goal is to include 1 to 3 perforators to optimize perfusion. In some cases, the DIEP flap may be converted to a muscle-sparing flap to achieve adequate arterial inflow and venous outflow to the tissue flap. Because the primary outcome is to look at perfusion of the flap most distant from the perforating vessels, in most cases, unilateral breast reconstructions will be performed, and perfusion zones 1, 2, and 3 included, according to the Holm classification (Figure 2). However, in patients with bilateral reconstructions, only Holm zones 1 and 2 will be included in a single flap. The supplying deep inferior epigastric vessels will be harvested at the level of the iliac artery and vein, and a microvascular anastomosis will be performed with the internal mammary artery and vein under a surgical microscope. A single artery and vein will be routinely anastomosed.

#### Approved Protocol

A tissue oximeter device (SnapshotNIR; Kent Imaging) will be used for all patients. This is a portable noninvasive monitor that measures tissue oxygen saturation using NIRS technology with the capability of saving images to allow for subsequent analyses. Measurements will be taken by holding the monitor at a standardized (30 cm) distance from the skin area where the oxygen levels are to be measured. Upon admission to the OR, preoperative baseline measurements (with patients breathing ambient air without supplemental oxygen) will be recorded over the abdominal flap tissue, followed by recordings immediately postinduction, 1-hour postinduction, when the abdominal flap is free (and still perfused by the chosen perforator arteries), before clamp removal postarterial reanastomosis, and 45 minutes following reanastomosis. All research personnel dedicated to this study will receive prestudy training on the perfusion zones and study outcomes to ensure that oxygenation measures are consistently taken from the same surgical region in relation to the perfusion zones (as described in Figure 2) throughout each case. In addition, the surgical team, led by authors [name], will assist with guiding the intraoperative oxygenation measurements with respect to flap location. However, the surgical team and attending anesthesiologist will be blinded to the Kent oxygenation measurements throughout the perioperative period, and surgery will be guided as per the standard of care. The ischemic period during which the flap is transferred (reflected by a fall in the oxygen saturation of the flap [23]) as well as the time of flap revascularization (characterized by increased oxygen saturation [23]) will be recorded. Upon completion of the surgical procedure, another NIRS-based monitor (Somanetics INVOS 5100C Cerebral/Somatic Oximeter; Medtronic) may be applied to the freshly reconstructed graft at the surgeon’s discretion. If deemed appropriate, a sticker will be applied over the flap for continuous graft oxygenation monitoring up to 48 hours postoperatively. However, if the surgeon requires the entirety of the graft to be exposed for visual monitoring (as per the standard care), a sticker/sensor will not be applied. Nevertheless, postoperative measures will be routinely recorded at 1, 2, 4, and 8 hours postoperatively, as well as on the morning of postoperative days 1 and 2 using the Kent device. All measures will be consistently taken at the same location [24]. Note that continuous intraoperative monitoring with the Somanetics INVOS Oximeter is not possible, as the sensors cannot be sterilized.

All surgical procedures will be performed by one of the 2 surgeons ([name]) to minimize variability in patient selection and surgical technique, both predictors of clinical outcomes in microsurgery [25]. Elective DIEP flap surgical procedures and anesthetic management will be completed in accordance with the standard of care. Perioperative management will be identical in both groups, apart from the hemodynamic monitoring for guiding intravenous fluid therapy and interventions as described below. In the OR, the ambient temperature will be set at 20^o^ C and standard monitors will be applied. Invasive monitoring in the form of an arterial line will be established as per the current practice. General anesthesia will be induced with propofol and fentanyl, followed by rocuronium to facilitate endotracheal intubation, and maintained with end-tidal sevoflurane (Et_sevo_=1.5%-3%) and additional doses of fentanyl and/or hydromorphone administered at the discretion of the attending anesthesiologist. Extra doses of rocuronium will be administered throughout the case for muscle relaxation. A mean arterial pressure (MAP) ≥65 mmHg will be targeted throughout the perioperative period. Likewise, all patients will receive standard measures to maintain oxygen saturation (SpO_2_ ≥95%), end-tidal carbon dioxide (Et_CO2_) between 35 and 40 mmHg, hemoglobin (>8 g/dl), and a heart rate <100 beats per minute (BPM). A warming device (enFlow IV Fluid/Blood Warming System; GE Healthcare) will be used for intravenous fluids, along with a forced-air patient warming system (Bair Hugger Normothermia System; 3M) to maintain normothermia (core temperature between 36 and 37.5 ^o^C). Arterial blood gasses will be checked every 2 hours (or more often at the discretion of the attending anesthesiologist) to specifically monitor the pH, SpO_2_, partial pressure of oxygen (PaO_2_) in arterial blood, partial pressure of carbon dioxide (PaCO_2_) in arterial blood, base excess, hemoglobin, and lactate levels as surrogates for tissue perfusion perioperatively. Urine output will be recorded hourly. The total amount of vasopressor, perioperative fluid (crystalloids and albumin 5%), and blood products, if any, will be recorded. In addition, the following demographic and surgical characteristics will be included: age, BMI, preoperative hemoglobin and hematocrit levels, American Society of Anesthesiologists (ASA) classification, Charlson Comorbidity Index, and total surgical and anesthetic time. Subsequently, 4 mg prophylactic intravenous dexamethasone upon the induction of general anesthesia and 4 mg ondansetron 15 minutes prior to completion of the surgical procedure will be administered to prevent nausea and vomiting. All patients will be managed postoperatively in a high-dependency unit (level 2 critical care) and given an intravenous patient-controlled analgesia (IV-PCA) pump containing hydromorphone (or an alternative in the case of adverse reactions) for postoperative pain management, as per the current standard of care. The postoperative goals (up to 48 hours postoperative) will be similar to the intraoperative period, namely: MAP ≥65 mmHg (or within 20% of baseline), SpO_2_ ≥95%, PaCO_2_ between 35 and 45 mmHg, hemoglobin >8 g/dl, core temperature between 36 and 37.5 °C, and heart rate <100 BPM. Research personnel will call patients 30 days postoperatively to document any complications, hospitalizations, and overall satisfaction. If patients cannot be reached via telephone, the patient’s family physician may be contacted and their medical record accessed to determine whether the patient experienced postoperative complications or required medical attention (as per the informed consent form).
